### Recruitment of study participants

We will recruit people who access domiciliary care by using two different approaches, based on (1) whether people access care through a homecare agency or housing with a care setting or (2) whether people directly employ a PA.

For people accessing care via a homecare agency or housing with care setting, we intend to recruit 1050 participants through their registered care location. Care locations are recruited with the help of study stakeholders, including the Homecare Association, Housing LIN, NIHR Regional Research Delivery Networks, Skills for Care and the Care Quality Commission. We aim to recruit approximately 100 homecare agencies and 50 housing with care sites across England, ideally clustered in about 30 local authorities across four regions: Yorkshire and the Humber, East Midlands, West Midlands and the South East. The care provider recruitment was initiated in May 2025. We will collect key provider characteristics through a short online survey completed by managers of care locations registering to participate in the study in November 2025 to January 2026. We will distribute survey packs to their clients in February 2026. Based on previous work, we expect around 800 responses from people accessing care via a homecare agency and 250 responses from housing with care residents.

With respect to care recipients directly employing PAs, we intend to recruit 800 participants. Recruitment will take place through Mark Bates, a specialist insurance company that holds contact details of a large number of PA employers. This approach is successfully used by Skills for Care, one of our study partners, for their annual survey of PAs and PA employers. Survey packs will be sent to approximately 17 500 PA employer email addresses.

Participants who access domiciliary care will be asked to involve their unpaid carers, should they have such support. Not all participants will have unpaid care support, and some unpaid carers may not wish to participate. Based on previous studies that adopted the route of recruiting carers via adults with care and support needs, we (conservatively) anticipate collecting responses from approximately 400 unpaid carers.^39^

Survey packs to people accessing care via a care location and to people who are employing a PA will include (1) a cover letter/invitation email, (2) a participant information sheet for care recipients and one for unpaid carers, (3) the care recipient and unpaid carer questionnaires, (4) a study privacy notice and (5) two free post envelopes.

Participants will be offered the option to (1) complete a hardcopy (paper) version of the questionnaire (alone or with help), (2) complete an online version of the questionnaire (alone or with help) or (3) arrange a telephone or face-to-face interview. By providing a number of options, we are hoping to accommodate the participants’ needs and to be as inclusive as possible.

Care locations are offered financial compensation for participation in the study in accordance with the NIHR Schedule of Events Costing Attribution Tool. Also, care recipients and unpaid carers returning completed questionnaires will be offered high-street vouchers as a thank you. The value of high-street vouchers is based on NIHR guidance for payments to public contributors in research.

### Sample size calculations

Sample sizes were determined using power calculations based on differences in means of ASCOT QoL scores between groups of LTC recipients, using Adult Social Care Survey (ASCS) 2021 data. Despite its limitations (eg, it does not include people self-funding their care and does not allow the identification of homecare recipients but only people accessing a broader range of community-based services), ASCS is the largest dataset capturing outcomes of people accessing LTC in England.

For the comparative analysis between people accessing homecare and care home residents, we would expect a difference in QoL scores of <0.1 (on a scale from 0 to 1). For detecting a statistically significant difference in QoL of 0.05 and considering an SD of QoL scores of 0.189, power calculations with alpha of 0.05 and power of 80% show that we would need a minimum sample of 226 observations in each group. The comparative cost-effectiveness analysis with care home residents will need to include homecare recipients with higher levels of care needs (ie, equivalent to care needs of care home residents). Allowing for three levels of care needs for the homecare recipients group (ie, low, medium and high) and taking into account that we will not be able to control during fieldwork how many respondents will be in each care need subgroup, we rounded up the target sample of homecare recipients to 800.

For the comparative analysis between homecare agency clients and PA employers, we expect a difference in QoL of 0.02 to 0.03. For detecting a statistically significant difference in QoL and considering an SD of QoL scores of 0.188, power calculations with an alpha of 0.05 and power of 80% show that we would need a sample of between 616 and 1389 observations in each group. To avoid setting unrealistically high target samples (and increasing research costs), we aim for a similar sample of 800 PA employers, as determined in the previous step for homecare agency clients.

The very limited information on care outcomes of housing with care residents is from findings of the Adult Social Services Environments and Settings (ASSET) and the Outcomes of Social Care for Adults (OSCA) studies, which found QoL scores of around 0.90. We based the power calculation (with an alpha of 0.05 and power of 80%) on an expected difference in QoL of 0.05 and SD of 0.189, leading to a minimum sample of 226 housing with care residents, which we rounded up to 250.

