We will also collect information on factors likely related to both care intensity and care outcomes, namely confounders. These include individual and household characteristics like age, gender, ethnicity, underlying health issues, difficulties with performing activities of daily living (ADLs), household composition, financial situation, the availability of home adaptations and general housing conditions and access to the local area and facilities. In addition, we collect information about the characteristics of the care recipients’ registered care location, namely type of service, sector and ownership; size; staffing levels; pay and employment conditions; characteristics and needs of people supported and commissioning practices of the local authorities they have contracts with, as well as the latest Care Quality Commission rating and date.

To reduce costs and avoid duplication, data on care home residents will come from the *Developing Resources and Minimum Data Set for Care Homes’ Adoption* (DACHA) study (NIHR127234). The design of survey questionnaires for this study has been informed (among others) by the structure of the data and variables collected in the DACHA project to make sure they are aligned for the comparative cost-effectiveness analysis between homecare and residential care. For example, the DACHA dataset includes information on care home residents’ QoL (collected using ASCOT Proxy), residents’ individual characteristics and care needs (eg, ADLs) and care home characteristics. The dataset includes a sample of about 679 residents from 34 care homes in England.^33^

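### The minimum sample sizes assume independent respondents although three of the four groups are clustered in providers, so at those minimums power is below the stated 80%

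*Protocol article*

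**What the plan says.** All sizes in the protocol article's section on sample size calculations come from differences in mean ASCOT scores.

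- **Homecare against care homes.** The inputs are a "difference in QoL of 0.05 and considering an SD of QoL scores of 0.189", and "power calculations with alpha of 0.05 and power of 80% show" that "we would need a minimum sample of 226 observations in each group". The homecare target is then raised to 800 to allow for three levels of care need.
- **Agency clients against PA employers.** Here "we expect a difference in QoL of 0.02 to 0.03", "considering an SD of QoL scores of 0.188", which leads to 616 to 1389 per group. The target is 800 in each group, with cost given as the reason for not going higher.
- **Housing with care.** The same 0.05 and 0.189 are used, "leading to a minimum sample of 226 housing with care residents, which we rounded up to 250".

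No ICC, design effect or other allowance for clustering appears, and neither the rise to 800 nor the rise to 250 is attributed to it.

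On how respondents are reached, the section on recruitment says "We aim to recruit approximately 100 homecare agencies and 50 housing with care sites across England", with about 800 and 250 responses expected from them. Under data requirements, the care-home data are "a sample of about 679 residents from 34 care homes in England". PA employers are approached individually through an insurer's contact list.

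**The concern.** People served by one agency, housing site or care home share staff, management and local conditions, so their scores are likely to be correlated. The protocol itself expects providers to matter: it collects provider staffing, pay and ratings as confounders, and it offers providers benchmarking of their care outcomes. A calculation that sets within-provider correlation to zero sits badly with this.

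What is at stake is the meaning of the minimums. The discussion treats missing the minimum sample requirements as the main threat to finding real differences. If the minimums are too low, reaching them gives false assurance, and a null result on mode or setting of care could be read as evidence of no difference.

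**Working it through.** **1. Reproduce the stated sizes.** Two-sided alpha 0.05, power 80%, equal groups, independent observations: n per group = 2 × [(1.960 + 0.842) × SD / d]².

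- d = 0.05, SD = 0.189: 224.3; the t-test version gives 225.3, so 226. Stated: 226.
- d = 0.03, SD = 0.188: 616.5. Stated: 616.
- d = 0.02, SD = 0.188: 1387.1; the t-test version gives 1388.0. Stated: 1389.

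All agree to within rounding at a design effect of exactly 1. One-sided versions (177, 486, 1093) do not match.

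**2. Average cluster sizes.** These are averages of expected or available respondents, not a sampling rule.

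- Agencies: 800/100 = 8
- Housing sites: 250/50 = 5
- Care homes: 679/34 = 20.0
- PA employers: 1 (not recruited through providers)

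**3. Power with clustering.** DE = 1 + (m − 1) × ICC for each group, and power = Φ(d / (SD × √(DE₁/n₁ + DE₂/n₂)) − 1.96). The documents give no ICC, so the range below is assumed.

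Example: 226 housing against 226 homecare at ICC 0.05. DE is 1 + 4 × 0.05 = 1.20 and 1 + 7 × 0.05 = 1.35. The standard error is 0.189 × √(1.20/226 + 1.35/226) = 0.02008. Power is Φ(0.05/0.02008 − 1.96) = Φ(0.53) = 70%.

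**4. Power at the stated minimum sizes**

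| Comparison | ICC 0 | 0.01 | 0.05 | 0.10 |
|---|---|---|---|---|
| 226 housing v 226 homecare, d = 0.05 | 80% | 78% | 70% | 62% |
| 226 homecare v 226 care home, d = 0.05 | 80% | 75% | 59% | 46% |
| 616 agency v 616 PA, d = 0.03 | 80% | 79% | 73% | 67% |
| 1389 agency v 1389 PA, d = 0.02 | 80% | 79% | 73% | 67% |

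The table uses cluster sizes of 5, 8 and 20. If 226 respondents were instead spread over all the providers (2.3 per agency, 4.5 per site, 6.6 per home), the first row becomes 79%, 76% and 71% at the three positive ICCs, and the second 79%, 74% and 68%. The loss is smaller but still present.

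**5. Power at the planned targets**

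| Comparison | ICC 0 | 0.05 | 0.10 | ICC at which power reaches 80% |
|---|---|---|---|---|
| 250 housing v 679 care home, d = 0.05 | 95% | 86% | 76% | 0.078 |
| 800 agency v 800 PA, d = 0.03 | 89% | 84% | 78% | 0.085 |
| 267 high-need homecare v 679 care home, d = 0.05 | 96% | 89% | 81% | 0.108 |
| 250 housing v 800 homecare, d = 0.05 | 95% | 91% | 85% | 0.148 |
| 800 agency v 800 PA, d = 0.02 | 57% | 50% | 45% | never at 80% |

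The 267 assumes that one third of the 800 homecare respondents have high needs and are spread over all 100 agencies (2.67 each).

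**The case against.** The strongest reply is that the study does not plan to stop at the minimums. The targets are 800, 800 and 250, with 679 residents already in the care-home dataset. At an ICC of 0.05 the four comparisons at differences of 0.05 and 0.03 keep about 84% to 91% power, and a real shortfall needs an ICC of roughly 0.08 or more, which the documents neither give nor exclude. This stands, and it limits the point to the stated minimums and to what the article should report about the targets.

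Four stronger readings are tempting but not supported.

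- **Power is lost at very small ICCs.** The effective size of 250 housing residents drops below 226 at an ICC of (250/226 − 1)/4 = 0.027, and that of 800 agency clients below 616 at (800/616 − 1)/7 = 0.043. These mark one group passing the per-group minimum of an equal-sized comparison. They are not where planned power falls below 80%, because the other group is larger or unclustered.
- **The study will report false significant differences.** A missing design effect in planning costs power. The article does not say that standard errors will assume independence, and how they are computed may properly be left to an analysis plan.
- **Everything sits in about 30 local authorities.** That figure describes the intended agencies and housing sites only. The care-home data are external and PA employers come from all of England.
- **Clustering explains the weak power at 0.02.** It is 57% with no clustering, and the article openly accepts a target below 1389.

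**Conclusion.** The point holds for the stated minimum sizes. They exclude any allowance for clustering, and every planned comparison has at least one provider-clustered group, so any realistic positive ICC puts power at those sizes below 80%: about 75% to 79% at an ICC of 0.01 and 59% to 73% at 0.05, taking the average cluster sizes. Because the printed figures themselves leave no room for an inflation, this is not merely detail that an article omits.

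At the planned targets the point is milder: most comparisons keep 80% up to moderate ICCs. The sizes rest on an assumed ICC range, one ICC common to both groups in a comparison, equal cluster sizes and a simple comparison of means. Matching, instrumental-variable estimation and any local-authority clustering are not included. The minimums should be corrected, but the design is not undermined.

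**What to change.** In the section on sample size calculations:

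1. Apply 1 + (m − 1) × ICC to each provider-clustered group (m about 8 for agencies, 5 for housing sites, 20 for care homes) and leave PA employers uninflated.
2. Estimate the care-home ICC from the existing care-home dataset, and show a range, for example 0.01 to 0.10, for the agency and housing groups.
3. Restate the minimum sizes. For scale, 226 becomes 236, 272 or 317 at m = 5, and 242, 306 or 385 at m = 8, for ICCs of 0.01, 0.05 and 0.10.
4. Report, for each planned comparison, the power or the detectable difference at the fixed targets, and say plainly that 0.02 is not adequately powered at 800 per group under any ICC.

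The cost is a recalculation and a revised paragraph. Stated detectable differences become somewhat larger; no extra recruitment is needed.

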### Inclusion criteria

Care recipients must be adults (ie, 18 years or over), accessing domiciliary care through a homecare agency or housing with care scheme (eg, extra care housing) or by employing a PA in England. Unpaid carers must be adult family members, partners or friends supporting a care recipient participating in the study.

All participants must have the mental capacity to consent. Our approach to mental capacity is informed by the following Mental Capacity Act principles: (1) every adult has the right to make decisions for themselves, and it must be assumed that they are able to make their own decisions unless it has been shown otherwise and (2) every adult has the right to be supported to make their own decisions. All reasonable help and support should be given to assist a person to make their own decisions and communicate those decisions before it can be assumed that they have lost capacity.

Our intention is to be as inclusive as possible in relation to people’s abilities and needs; however, we will instruct care providers to exclude people who lack the mental capacity to consent, based on their records of LTC assessment, having a court-appointed deputy or being under a Deprivation of Liberty Safeguard. We will also exclude PA employers who have an additional nominated adult (eg, a legal guardian) on their employer liability insurance.

### Consent

The way a participant’s consent will be recorded will depend on the option chosen by the participant to respond. More specifically, for the online version of the questionnaire, participants will be required to provide consent online before accessing the online questionnaire. For the hardcopy version of the questionnaire, the consent form will be included at the beginning of the questionnaire booklet, and participants will be asked to read it before completing the survey. It will be made clear that by completing and returning the hardcopy version of the questionnaire, people are consenting to participate in the study. For the telephone interview, the interviewer will offer to read out the participant information sheet and the consent form over the phone, and consent will be recorded before completing the questionnaire. Finally, for the face-to-face interview, a similar procedure will be followed, and the participant will be invited to sign a consent form.

### Data analysis

We will conduct separate cost-effectiveness analyses of domiciliary care across levels of care need (or care intensity), types of domiciliary care (eg, homecare agencies vs direct employment of PAs) and care settings (ie, domiciliary care vs housing with care vs care home services).

As mentioned earlier, we will adopt a ‘production function’ approach to estimate the cost-effectiveness of domiciliary care and use IV to address potential selection bias of care intensity with respect to unobserved factors.^13 14^

The IV method can be understood as a two-stage process. The first stage models the endogenous independent variable (ie, in our case, formal care inputs) as a function of so-called instruments and other observed characteristics. The second stage then models the outcome variable (ie, QoL) as a function of predicted values from the first stage model and the observed characteristics. Under the assumptions that the instruments are unrelated to unobserved confounders and enter the second-stage model only via the independent variable of interest (ie, affect care recipients’ QoL only through the formal care services), estimates will give the unbiased causal effect.^40^

The challenge of the IV method is to find ‘good’ instruments, namely variables (highly) correlated with care recipients’ formal care but otherwise unrelated to their QoL and other outcomes of interest. An instrument that worked well in previous studies relies on variation in local authorities’ LTC policy.^13 14^ Local authorities in England have a significant degree of autonomy in designing and commissioning LTC services tailored to population needs and local market circumstances. They also differ in the level of financial resources available to them through externally determined central government grants and council tax (ie, a tax on housing) revenue. As a result, commissioning can often differ between local authorities, and two people with the same care needs and circumstances but residing in different local areas can receive different levels of support.^13 14^ To leverage this policy variation, the above studies specified the leave-one-out average level of formal care input among individuals in a local area as the IV. This measure, also known as a spatial lag, relies on correlation between individuals’ formal care use and the level of care in their local area and is expected to be uncorrelated with unobserved individual-level confounders.

An alternative to the production function approach for identifying the impact of LTC services on care recipients’ QoL applies a counterfactual self-estimation method. ASCOT-INT4 asks participants to report both their QoL at the time of survey but also their ‘expected’ QoL in the hypothetical situation in which they would not have access to LTC services. This allows the calculation of self-reported QoL gain (ie, impact of services). Although subject to its own limitations, the methodology has been shown to be feasible and to provide similar estimates to the IV method.^30^ Therefore, where possible, we will compare these results to those of the IV analysis. Ideally, where cost-effectiveness estimates using both approaches coincide, this could provide evidence of the robustness of our findings. Where estimates differ, the direction and size of the discrepancy can also be assessed to further understand the limitations of the two approaches.

For comparative cost-effectiveness analysis between care settings, the most common approach to address the issue of self-selection bias is using matching techniques like, for example, Propensity Score Matching.^24 41 42^ By matching individuals with similar observed characteristics from the two groups (eg, gender, age, ethnicity, underlying health issues and difficulty with ADLs), the differential effect of the care services on care recipients’ QoL can be identified if assignment to groups is random conditional on controls.^43^

The same matching technique can be used for the comparative analysis between modes of domiciliary care.

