### Aims and objectives

The main aim of the study is to evaluate the value for money of domiciliary care. In this respect, we will assess the comparative cost-effectiveness between:

People with different levels of care needs;Modes of delivery (eg, homecare agencies vs directly employed PAs);Different care settings (ie, residential care and housing with care).

To capture the broader societal impact of domiciliary care, we will assess its effects on healthcare demand (eg, potentially avoidable hospitalisations) as well as on unpaid carers’ quality of life (QoL) and other outcomes (eg, health and formal employment).

To deliver our aim and objectives, we have organised the study in four work packages, as shown in the flow diagram in figure 1.

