### Cost-effectiveness

The estimated impact of formal care input on QoL can be seen as the marginal change in utility (ie, marginal utility $u_{k}$) arising from a marginal change in formal care input k. Care input can be measured as cost-weighted services (eg, hours of home care multiplied by gross unit costs $c_{k}$), allowing the estimation of incremental cost-effectiveness ratios, as marginal costs per marginal utility ($c_{k}/u_{k}$). Incremental cost-effectiveness ratios can be compared between different levels of care intensity, with lower values representing greater efficiency (ie, better value for money). This is relevant for informing policy questions, such as how much potential gain additional funding can achieve or how best to allocate limited budgets across different alternative services.

We also position unpaid carers as beneficiaries of care and consider the cost-effectiveness of LTC services for unpaid carers. This expands the literature on the ‘spillover effects’ of LTC services on carers to consider that services can be targeted ‘at’ or ‘for’ carers and/or jointly for supported people and their carers, based on the whole family (sometimes, known as the ‘dyadic’) approach. See the next section for more details.

Additional considerations that would generalise cost-effectiveness implications are on the interdependency between the health and LTC systems. Existing research has explored, for example, the impact of LTC spending on health service use,^44^ and our stakeholder consultation also revealed an interest in these associated effects. We will assess the effects of LTC provision on avoidable hospitalisations (ie, effects on demand for healthcare) in the analysis. However, we gave these aspects less focus, as we regard them as additional to the main aims of LTC, which is to improve the social care-related QoL of care recipients and their carers.

Differential effects between care alternatives (eg, modes of domiciliary care or care settings) will be captured by the coefficient of the (binary) ‘treatment’ variable (eg, the setting or mode of interest over an alternative) in the matching models. These coefficients will provide the average difference between the ‘treated’ groups’ actual QoL and their QoL if they would have received the alternative type of care (ie, the average treatment effect on the treated).

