## Discussion

This study aims to determine the impact of domiciliary care on the QoL of people accessing care and their unpaid carers, as well as the value for money provided by domiciliary care services compared with other forms of LTC.

We will survey 1850 people accessing domiciliary care and 400 unpaid carers. A ‘production function’ approach will be used to estimate the cost-effectiveness of care services and an IV method to address potential selection bias of care intensity with respect to unobserved confounders. The study adds to previous findings by analysing data from a larger and more diverse sample of people accessing domiciliary care, people accessing different forms of domiciliary care and accounting for the role of care provider characteristics. Our contribution to the impact of domiciliary care services on unpaid carers will be through comparisons not covered in previous studies (eg, different forms of domiciliary care, types of housing, as well as sources of funding).

The main research question addressed is how much QoL gain can be attained if an additional unit of a specific type of care, for example, an hour of contact of domiciliary care, is made available? This focus on the incremental cost-effectiveness of services is relevant for informing policy questions, such as the extent to which additional funding can increase potential gains or how best to allocate limited budgets across different alternative services. This focus aligns with the needs of and feedback from policy stakeholders and the funder.

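### The two stated IV assumptions do not yield the unbiased causal effect: the slope is at best a consistent estimate of an effect weighted towards people whose hours follow local provision, and the plan does not say so

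*Protocol article*

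**What the plan says.** In the protocol article, Data analysis describes IV as two stages and gives its conditions: "Under the assumptions that the instruments are unrelated to unobserved confounders and enter the second-stage model only via the independent variable of interest". It concludes that "estimates will give the unbiased causal effect". The next paragraph adds relevance, since good instruments are "variables (highly) correlated with care recipients" and their formal care. The instrument it describes from earlier studies is "the leave-one-out average level of formal care input among individuals in a local area as the IV", which draws on differences in local authority policy.

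Several passages leave room for effects to differ between people:

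- Aims and objectives lists "People with different levels of care needs" first among the groups to be compared.
- Data analysis opens with "We will conduct separate cost-effectiveness analyses of domiciliary care across levels of care need (or care intensity"; the bracket closes there.
- Cost-effectiveness says "Incremental cost-effectiveness ratios can be compared between different levels of care intensity".

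The Discussion puts the main research question as "how much QoL gain can be attained if an additional unit of a specific type of care" is made available, and names no population. For the matching models, the Cost-effectiveness section does name the target: the average treatment effect on the treated. It names none for IV.

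**The concern.** Independence, exclusion and relevance identify a single causal effect only if an extra hour of care does the same for everyone. Otherwise the IV slope is a weighted average, with weights set by the first stage. It is a sensible average only if nobody's hours move against the instrument. No section states constant effects or one-directional response, and the limitations paragraph of the Discussion, which covers sensitivity to the instrument and to functional form, does not mention differing effects.

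Two readings of the results depend on this:

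- **The main question.** A slope that belongs to people whose hours follow local provision could be reported as the gain per hour for recipients in general. The cost-effectiveness ratio, marginal cost over marginal utility, would carry the same label.
- **The comparison with self-estimated gain.** Data analysis treats agreement between the two methods as possible evidence of robustness, and disagreement as informative about their limitations. Self-estimation averages over respondents, while IV weights by response. The two can differ when both are valid, or agree when one is biased.

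**Working it through.** **Inputs from the protocol article.** The stated IV conditions, the described instrument and the planned comparisons are as set out above. The Introduction puts self-funders at 23% of community-based care recipients. The article gives no gain per hour and no first-stage coefficient, so there is no stated figure to reproduce. All gains and responses below are assumptions.

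**Step 1: what the slope estimates.** Let b be a person's QoL gain per hour and π the response of their hours to the instrument. With a valid instrument, in large samples,

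IV slope = E(πb) / E(π) = E(b) + Cov(π, b) / E(π).

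The gap from the average gain E(b) is therefore Cov(π, b) / E(π). It is zero if gains are equal, if responses are equal, or if the two are uncorrelated. If π is negative for some people, they receive negative weight, which is why a one-direction assumption is needed. In a finite sample the estimator is not unbiased even with constant gains.

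**Step 2: illustration with three equal need groups (low, medium, high).** The slope is Σ(share × π × b) / Σ(share × π), taking the instrument's variance as equal across groups. The equal shares cancel.

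| Assumed gain per hour | Assumed response | IV slope | Average | Gap |
|---|---|---|---|---|
| 0.002, 0.005, 0.008 | 1, 1, 1 | 0.015/3 = 0.0050 | 0.0050 | 0 |
| 0.002, 0.005, 0.008 | 0.2, 0.5, 1 | 0.0109/1.7 = 0.0064 | 0.0050 | +28% |
| 0.002, 0.005, 0.008 | 1, 0.5, 0.2 | 0.0061/1.7 = 0.0036 | 0.0050 | −28% |
| 0.006, 0.003, 0.001 | 2, 1, 0.5 | 0.0155/3.5 = 0.0044 | 0.0033 | +33% |
| 0.006, 0.003, 0.001 | 0.5, 1, 2 | 0.0080/3.5 = 0.0023 | 0.0033 | −31% |
| 0.004, 0.003, 0.002 | 2, 1, 0.5 | 0.0120/3.5 = 0.0034 | 0.0030 | +14% |
| 0.004, 0.003, 0.002 | 0.5, 1, 2 | 0.0090/3.5 = 0.0026 | 0.0030 | −14% |

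Because the ratio is c/u, at equal hourly cost a slope 28% above the average makes cost per gain 1/1.28 = 0.78 of its average-based value, and a slope 28% below makes it 1/0.72 = 1.39 times that value.

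**Step 3: simulation check of the first three rows.** With 3,000,000 records, a valid instrument and an unobserved confounder, the need-adjusted pooled slopes were 0.00504, 0.00641 and 0.00366. IV fitted separately by need gave (0.00203, 0.00502, 0.00806), (0.00253, 0.00496, 0.00792) and (0.00211, 0.00510, 0.00780). These match the assumed 0.002, 0.005 and 0.008 apart from simulation error, which is larger where response is weak.

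**Step 4: weighting that separate fits by need leave in place.** Suppose the 23% who self-fund do not respond to local authority policy, and their gain per hour is r times that of the others. The IV slope divided by the overall average is then 1 / (0.77 + 0.23r). For r = 0.5 this is 1/0.885 = 1.13; for r = 1 it is 1; for r = 2 it is 1/1.23 = 0.81.

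**The case against.** The strongest reply is that the plan does not set out to report one overall slope. Data analysis opens by promising separate analyses across need, and Step 3 shows that IV fitted by need recovers each group's gain. That stands. A reader might infer that a single slope across all need levels is planned, but no section says so. The words about care intensity leave open whether the separate analyses are IV models by need, and that detail can properly sit in a fuller plan.

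A reader might also infer that the aim presupposes differing effects, so that the plan contradicts itself. It does not: the aim is to assess whether cost-effectiveness differs. The plan allows differing effects, and that is all this point needs.

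Third, the weighted effect may be the useful one. The Discussion ties its question to what additional funding could achieve, and people whose hours move with local provision are arguably the right group for that. This is a fair argument for keeping the estimand, and so for naming it. It also counts against requiring slopes to be re-averaged over need shares, which would be a preference about the target. Need-by-instrument terms would also risk weak instruments, since agency and housing recruitment is meant to cluster in about 30 local authorities.

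Finally, the plan admits that IV is sensitive to instrument specification and promises to test validity, underlying assumptions and functional form. Those commitments help, but they do not say whose effect the slope measures.

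**Conclusion.** The sentence claims a property that the method lacks. Under the stated conditions plus relevance, and with responses in one direction, the IV slope is a consistent estimate of an effect weighted towards people whose hours follow local provision. It need not equal the average gain per hour among all recipients.

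The size of any gap cannot be determined from the documents. Under the assumed inputs it ran from 31% below to 33% above the average, with 14% either way for milder differences and zero when response was equal across groups. Even its direction depends on inputs that the documents do not give. It would be wrong to infer that the study's estimate will be off by these amounts, or that it must differ from the average at all. The finding concerns a stated property and an unnamed estimand. It assumes that the instrument used is the local-provision measure described, or one like it.

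**What to change.** In Data analysis, replace the claim of an unbiased causal effect with wording such as: a consistent estimate of a weighted effect among people whose hours follow local provision, assuming hours respond to the instrument in one direction.

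Then carry that estimand through:

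- In the Discussion, answer the main research question for that group, not for recipients in general.
- In the comparison with self-estimated gain, say that the two methods may differ only because they average over different people, and that agreement alone does not establish validity.
- Where IV is fitted by need level, as the promised separate analyses suggest, report each level's first-stage coefficient so readers can see whose hours respond. Weighting within a level, for example by funding source, remains and should be acknowledged.

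This needs no new data and little extra analysis. The cost is a narrower stated conclusion.
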